### Intervention trials 1 and 2 treatment outcomes

At each follow-up visit, children in the AM trials will receive one of the classifications listed in Table 2. Children will be assigned a final discharge outcome of recovery, defined as having a WLZ at two standard deviations below the median or better *and* MUAC at 125 mm or better *and* no edema, all for two consecutive visits. Children will be considered to have not recovered with any of the following discharge outcomes: deterioration to SAM (for children in the MAM trial), death, hospitalization, lost to follow-up, and remaining with AM after 16 weeks of treatment.

**Table 2 Tab2:** Follow-up visit outcomes for AM intervention trials

	SAM Trial	MAM Trial	Definition
**Interim Status**			
	Continued SAM	−	Anthropometry demonstrates ongoing SAM
	Improved to MAM	−	Anthropometry demonstrates improvement to MAM
	−	Continued MAM	Anthropometry demonstrates ongoing MAM
**Final Outcome = Recovered**			
	Recovered	Recovered	Anthropometry has reached recovery criteria for 2 consecutive visits within 16 weeks of enrollment
**Final Outcome = Not Recovered**			
	−	Deteriorated to SAM	Anthropometry worsened from MAM to SAM since previous visit
	Died	Died	Death since previous visit
	Hospitalization	Hospitalization	Child hospitalized for medical or nutritional deterioration
	Lost to follow-up	Lost to follow-up	Child unable to be located for three consecutive visits
	Remained with AM	Remained with AM	Child has not achieved recovery criteria after 16 weeks of therapy

### Intervention trials 1 and 2 sample size

The powered objective for the AM intervention trials will be the rates of anthropometric recovery by 16 weeks (Table 2), comparing each intervention group individually against the standard of care (control) group, based on the hypothesis that the novel interventions are non-inferior.

A 2020 systematic review of treatment outcomes among children treated for SAM as outpatients with the standard dosing of RUTF showed an average recovery rate of 70% [24]. In Ethiopia specifically, a recent study in Gondar found approximately 75% of children with SAM treated as outpatients recovered [25]. Another recent study in Oromia found that children enrolled by MUAC alone had a recovery rate of approximately 85% [26]. Less complete outcome data exists for children with MAM, but an operational study from southern Ethiopia demonstrated a 73% recovery rate for children with MAM treated with RUSF [27]. Based on these accumulated data, we have powered the study based on an anticipated recovery rate of 75% for both the SAM and MAM studies.

The non-inferiority margin that is considered clinically acceptable is a relatively subjective judgment that needs to incorporate local sociocultural preferences and economic considerations. Trial cost and duration limitations must also be considered. To help inform this decision, we conducted interviews with health care workers and community leaders within Ethiopia, as well as discussions with our technical advisory groups. There was consensus that a non-inferiority margin of 5–10% would be considered clinically useful, although there was a notable preference for as small of a margin as would be feasible to provide the most robust data, especially compared to prior trials of modified dosing regimens which have used comparatively larger non-inferiority margins. Given resource constraints, we will thus aim for a non-inferiority margin of 6% for each trial, but may have to compromise to up to 10% if enrollment challenges arise.

The α parameter (Type I error) will be set at 0.05, indicating a 5% risk of identifying a difference between an experimental group and the control group where none really exists. The β value (Type II error) will be set at 0.20, thereby giving a power of 80% to identify a difference between an experimental group and the control arm. Due to possible incorrect enrollments, incomplete or inaccurate data collection, and/or drop-outs, we will aim to enroll an additional 10% in each study arm beyond the sample size target calculation.

Based on these parameters, we determined that the minimum sample size needed for a non-inferiority margin of 6% is 798 children per study arm; the minimum needed for a non-inferiority margin of 8% is 462 children per study arm; for 10%, the minimum needed for 10% would be 305 [28]. Multiplying the largest of these by three study arms per trial gives a targeted sample size for enrollment of 2400 children in each trial. This warrants an enrollment of an average of 140 children per month in each trial. If enrollment is slower than anticipated, requiring an adaptation to the enrollment goal, then 1400 children in each trial will be sought to achieve a non-inferiority margin of 8% in a three-armed trial, or 915 for a 10% non-inferiority margin.

### Post-recovery– trial 3

Children from all 3 arms in each of the 2 AM intervention trials who achieve anthropometric recovery within 16 weeks of enrollment will then be offered enrollment into the third of the three integrated trials encompassed by the MODAM study (Fig. 1). This post-recovery trial aims to offer insights into numerous outstanding questions in the AM field, given that high rates of post-recovery relapse and mortality place heavy burdens on operational SAM and MAM treatment programs [16, 29]. High post-SAM relapse is a notable problem in Ethiopia, where such cases make up a high proportion of CMAM enrollments [30–32].

Among issues to be explored include the sustainability of anthropometric recovery following the various novel interventions being tested for SAM and MAM treatment, in addition to an investigation of other post-discharge health outcomes such as the overall growth trajectory over the subsequent six months. A major concern in the domain of modified dosages has been the possibility of decreased linear growth velocities among those children treated with proposed modified dosages which has been observed in some trials [21, 33], but not others [34]. These medium-to-long term outcomes are an important indicator to be considered in the overall quality of CMAM programs [35], especially those using novel dosing strategies [36].

Also to be investigated are whether certain post-recovery monitoring strategies are more effective in the medium-term (6 months) to improve early identification of relapse. The theoretical underpinning for the importance of early identification is that when children are less wasted, they are more likely to have better outcomes when readmitted for AM care, including higher likelihood of recovery, less time and resources needed for recovery, and less long-term growth faltering and morbidity. In addition to more frequent follow-up visits to monitor for relapse, some evidence has suggested that children’s caregivers are themselves able to successfully screen for low MUAC and edema at home, potentially providing earlier identification and diagnosis [37–40]. This is presumed to have the benefit of earlier entry into care, higher likelihood of rapid recovery, and less long-term consequences of AM.

For this third trial, children who recover will thus be enrolled in the post-recovery follow-up trial on the day of recovery from any arm of either of the intervention trials. They will be randomized using similar methods as described above into one of three different study arms and followed for 24 weeks:

• Standard of care (control) group. Children in this group will receive standard nutrition, infant and young child feeding (IYCF), and water, sanitation, and hygiene (WASH) education [20]. Caregivers will be educated to return to the health post or seek care from a HEW if they have a health or nutritional concern regarding their child. A single follow-up visit at 24 weeks after initial AM recovery (i.e., enrollment into the post-recovery trial) will be scheduled to assess anthropometry and nutritional status.

• Experimental group A: Active Follow-up. In addition to the interventions received by the control group, caregivers will be requested to revisit the health post/center for scheduled follow-up visits at 4,12, and 24 weeks after recovery. If a caregiver fails to attend the scheduled health post/center visit, then a HEW or study staff member travel to the child’s home to remind them to complete the scheduled follow-up visit the following week or directly collect the data at the home as a last resort. This group is considered to have the most “active” follow-up procedures implemented by healthcare workers and volunteers.

• Experimental group B: Family MUAC Follow-up. In addition to the interventions received by the control group, caregivers will receive training on how to implement home-based MUAC and edema screening, including provision of MUAC tapes [41]. Caregivers will be educated how and when to assess their child’s MUAC and edema, and to return for care if their child’s MUAC falls into the AM category, their child has bilateral pitting edema, or at any time they are concerned about their child’s overall health. These children will also be scheduled for a single follow-up visit at 24 weeks after initial AM recovery.

Whenever a child in the post-recovery trial, regardless of study arm, is brought back to the health post, anthropometry will be assessed by study staff to determine whether or not the child relapsed to AM as well as to record overall growth trajectory. An additional health and demographics questionnaire will be completed. Those identified with AM will then receive treatment per the standard national protocol and continued to be followed for a total of 24 weeks from the time of initial recovery as some may relapse multiple times.

### Post-recovery outcomes of interest

To help inform the assessment of the various novel treatment protocols, a number of parameters will be investigated over the 24-week post-recovery follow-up period, including, but not limited to:

• Vital and nutritional status, including rates of relapse to SAM and MAM, hospitalization, loss to follow-up, and mortality.

• Weight gain, as measured in g, g/kg/d, WAZ, and WLZ.

• MUAC gain, as measured in mm, mm/d, and MUAC-for-age Z-score (MUACZ).

• Length gain, as measured in cm, mm/d, and length-for-age z-score (LAZ).

• Rate, severity, and frequency of relapse and mortality.

The relative effectiveness of the three different post-recovery strategies will be investigated by assessing a number of parameters, including, but not limited to, the following:

• Frequency of return visits to the health post.

• History of hospitalizations.

• Frequency of identification of relapse to AM.

• Number of person-months with AM after initial recovery.

• Anthropometry at the time of relapse.

• Anthropometry at 24-week post-recovery.

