### Statistical analyses

Standard statistical approaches will be used in each of the three trials to analyze each intervention arm independently in comparison to the control arm. Dichotomous variables will be compared using Chi-square testing. Continuous variables will be analyzed using the Student t-test. Rates of recovery and relapse will be evaluated using Kaplan-Meier survival analyses. Regression analyses will be used as appropriate to control for confounding variables. In general, P values less than 0.05 will be considered statistically significant, although this will be reduced in the case of multiple comparisons. 95% confidence intervals will be calculated in addition to P values in order to provide additional detail about error margins in the various calculations. Intention-to-treat analyses will be used throughout, as this will provide the most pragmatic and applicable evidence to inform the real-world scale-up of these interventions.

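### The post-recovery outcomes used to assess the doses exist only for children who recovered, so these secondary dose comparisons are not intention-to-treat

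*Protocol article*

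**What the plan says.** All references are to the protocol article.

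- **Who is followed.** Under Post-recovery – trial 3, children from every dose arm "who achieve anthropometric recovery within 16 weeks of enrollment will then be offered enrollment into the third of the three integrated trials". The 24-week clock starts on the day of recovery. No follow-up is described for children whose treatment outcome is non-recovery.
- **What the follow-up is for.** The same section wants to explore the "sustainability of anthropometric recovery following the various novel interventions being tested for SAM and MAM treatment", and names slower linear growth under modified doses as a major concern. Post-recovery outcomes of interest then gives two lists. The first serves the dose question: "To help inform the assessment of the various novel treatment protocols, a number of parameters will be investigated over the 24-week post-recovery follow-up period". It covers relapse, hospitalisation, loss to follow-up, mortality, and weight, MUAC and length gain. The second list compares the three post-recovery strategies.
- **Analysis principle.** Statistical analyses states: "Intention-to-treat analyses will be used throughout".
- **Expected effect of dose.** The description of SAM experimental group B allows that this regimen may both lower recovery and raise relapse, and says this should be tested. For MAM experimental group B the article hopes for faster recovery and possibly better relapse rates and growth.

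**The concern.** Recovery happens after randomisation and is the outcome that dose is meant to influence. If doses differ in recovery, the recovered children in each arm are different selections from groups that were alike at randomisation. A dose that fails to bring the frailest children to recovery removes them from its own relapse denominator and can then appear to have the lower relapse rate. The reverse can also occur: a dose that brings more marginal children to recovery, as hoped for MAM group B, may look worse on relapse because it succeeded.

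What is at stake is the reading of the longer-term results. Durability of recovery and linear growth are the article's own stated concerns about modified dosing. Policymakers could read a recovered-only contrast as a randomised one, particularly as the article promises intention-to-treat analysis without exception.

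**Working it through.** **Inputs from the article**
- Recovery: "we have powered the study based on an anticipated recovery rate of 75% for both the SAM and MAM studies".
- Margin: "we will thus aim for a non-inferiority margin of 6% for each trial", with up to 10% allowed if enrolment is slow. A dose at the edge of the margin therefore recovers 75 − 6 = 69%, or 65% at the wider margin.
- Relapse after recovery: the Background cites more than one third; 1/3 is used here.
- About 800 children per arm.

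**Assumption not in the article**
- *q*, the relapse rate in the 6% of children who recover on the better dose but would not on the other. The range shown runs from 1/3 to 100%.

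**The plan's own figure.** The stated minimum for the 6% margin is 798 per arm. A two-proportion formula for 75% against 69%, α = 0.05 one-sided (the article does not state sidedness), power 80%, with continuity correction, gives 725; 725 × 1.10 = 798. For the 8% and 10% margins the same route gives 465 and 307, against the stated 462 and 305. The contrast of 75% with 69% is thus the one the sample size is built on.

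**Who leaves the comparison.** With 800 per arm, 0.75 × 800 = 600 and 0.69 × 800 = 552 children recover. The recovered-only comparison omits 200 and 248 randomised children.

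**Effect on relapse.** Let the 69% who recover on either dose relapse at 1/3 in both arms, so that dose has no effect on their relapse.
- Relapse among recovered, control = (0.69 × 1/3 + 0.06 × *q*) / 0.75
- Relapse among recovered, experimental = 1/3 = 33.3%
- Relapse-free sustained recovery per child randomised, control = 0.75 − (0.69 × 1/3 + 0.06 × *q*)
- The same, experimental = 0.69 − 0.69 × 1/3 = 46.0%

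Example with *q* = 0.60: (0.230 + 0.036)/0.75 = 35.5%, and 0.75 − 0.266 = 48.4%.

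| *q* | Relapse among recovered, control | Apparent benefit of experimental dose | Sustained recovery, control | True deficit of experimental dose |
|---|---|---|---|---|
| 1/3 | 33.3% | 0 | 50.0% | 4.0 points |
| 50% | 34.7% | 1.3 points | 49.0% | 3.0 points |
| 60% | 35.5% | 2.1 points | 48.4% | 2.4 points |
| 75% | 36.7% | 3.3 points | 47.5% | 1.5 points |
| 100% | 38.7% | 5.3 points | 46.0% | 0 |

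For *q* between 50% and 75% the two measures point in opposite directions. At 65% recovery the apparent benefit for *q* = 50%, 60% and 75% is 2.2, 3.6 and 5.6 points.

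**Second model.** Recovery and relapse are linked through a bivariate normal liability with an assumed correlation, and dose has no effect on relapse. At 69% recovery the apparent benefit is 0, 1.0, 1.8 and 2.9 points for correlations of 0, 0.3, 0.5 and 0.7. The order of size is the same.

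**Against sampling error.** For *q* = 0.60, the standard error of the relapse difference is √(0.355 × 0.645/600 + 0.333 × 0.667/552) ≈ 2.8 points. The bias is about one standard error or less over most of the range.

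**The case against.** The strongest reply is that the article fixes no formal recovered-only test of dose. The post-recovery parameters are to be investigated and explored, they are unpowered, and relapse can only be observed after recovery. The denominator of a secondary outcome is often left to an analysis plan. In the scenario above, the powered outcome would show the dose 6 points worse, so the harm would be visible there. All of this limits the weight of the point. It does not remove it, because the article itself fixes who is followed, that these data serve the dose assessment, and that every analysis is intention-to-treat. The three do not fit together.

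Four stronger readings are tempting, and the article does not support them:

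- **That mortality is compared by dose only among recovered children.** Table 2 counts deaths during treatment as non-recovery for all randomised children, and under Data and safety monitoring the DSMB compares mortality by arm. Only post-recovery mortality is restricted. Anthropometry is likewise taken at every treatment visit; the restricted growth outcomes are the post-recovery ones.
- **That trial 3 or its arms are compromised.** Children are randomised again at recovery, so the strategy comparison is sound. Trial 3 arm is balanced across dose arms in expectation, so it does not confound the dose comparison even though the arms differ in visit frequency.
- **That sustained recovery is absent from the plan.** Cost effectiveness analysis already costs children who do and do not sustain recovery, by study arm. What is missing is its use as the statistical comparison of doses.
- **That the bias is established.** It needs both a difference in recovery and a link between marginal recovery and later relapse. Neither is known.

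**Conclusion.** The point stands for the secondary dose comparisons of post-recovery relapse, growth and mortality. These condition on a post-randomisation outcome that the article itself expects dose may affect, and so they contradict its intention-to-treat statement. The powered recovery outcome, mortality during treatment and the trial 3 comparison are not touched.

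If recovery is 75% against 69% and marginal recoverers relapse at 50–75%, the recovered-only relapse rate favours the worse dose by about 1 to 3 points, while that dose is 3.0 to 1.5 points worse per child randomised. The relapse rate in marginal recoverers is an assumption. At the common rate of one third the bias is zero, and with equal recovery of the same kind of children it also vanishes. The size is modest; the concern is that the direction can be wrong and that a true increase in relapse of similar size could be hidden.

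**What to change.** 1. Make the between-dose comparison of post-treatment outcome **relapse-free sustained recovery**: recovered by 16 weeks, and alive with no relapse to acute malnutrition identified through the 24-week post-recovery visit. Use all children randomised in trial 1 or trial 2 as the denominator, and count non-recovery, death and any relapse as failure. Status at the 24-week visit alone would not do: the article expects relapsed children to be treated and followed on, so a child who relapsed and recovered again would count as a success.
2. State how recovered children who decline trial 3 or are not seen at 24 weeks are handled.
3. Label relapse, growth and mortality compared by dose among recovered children as descriptive and not protected by randomisation, and limit the intention-to-treat statement accordingly.
4. Adjustment for trial 3 arm is optional, for precision.

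The cost is wording and a small extra analysis. Every trial 3 arm already has a 24-week visit, so this endpoint needs no new follow-up. A fully randomised comparison of later growth or late mortality would need follow-up of the non-recovered children, which is why item 3 asks only for a label.

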### Statistical analyses

Standard statistical approaches will be used in each of the three trials to analyze each intervention arm independently in comparison to the control arm. Dichotomous variables will be compared using Chi-square testing. Continuous variables will be analyzed using the Student t-test. Rates of recovery and relapse will be evaluated using Kaplan-Meier survival analyses. Regression analyses will be used as appropriate to control for confounding variables. In general, P values less than 0.05 will be considered statistically significant, although this will be reduced in the case of multiple comparisons. 95% confidence intervals will be calculated in addition to P values in order to provide additional detail about error margins in the various calculations. Intention-to-treat analyses will be used throughout, as this will provide the most pragmatic and applicable evidence to inform the real-world scale-up of these interventions.

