**Fig. 1 Fig1:**
[figure not shown]
Patient flow through 3 individually randomized clinical trials encompassed by the MODAM study

• SAM standard of care (control) group: Children in this group will be dosed with approximately 150–200 kcal of RUTF per kg of the child’s weight per day (Table 1), reflecting the current national standard of care in Ethiopia [20]. In this dosing regimen, as the child’s weight increases over the course of treatment, so too does the amount of RUTF that is provided each week.

**Table 1 Tab1:** Weight-based dosing of 500-kcal RUTF sachets for children in the standard of care group

Weight (kg)	Sachets per day	Sachets per week
**3.5–3.9**	1½	11
**4.0–5.4**	2	14
**5.5–6.9**	2½	18
**7.0–8.4**	3	21
**8.5–9.4**	3½	25
**9.5–10.4**	4	28
**10.5–11.9**	4½	32
**≥ 12**	5	35

• SAM experimental group A: Children in this group will be dosed with two sachets of RUTF to consume daily until discharge. This reflects the draft simplified emergency protocol in Ethiopia and a common choice for novel protocols in many settings. In addition to the possibility of improved cost-effectiveness with this experimental dosing, the simplicity of a consistent dose each day could make it easier for health workers to implement, improve understanding among caregivers for how to ration a week’s worth of RUTF accurately, and improve the predictability of demand forecasting.

• SAM experimental group B: Children in this group will be dosed with two sachets of RUTF to consume daily while *any* of their anthropometric parameters are in the SAM range (i.e., WLZ < − 3, MUAC < 115, or edema). Children will then transition to one sachet of RUTF to consume daily when *all* of their anthropometric parameters are in the MAM range or better (i.e., WLZ ≥ -3, MUAC ≥ 115, and no edema). Similar dosing regimens have been previously trialed and piloted in other locations [21], with the same potential advantages of experimental group A. This dosing regimen also has the theoretical advantage of providing a higher dose of macronutrients and micronutrients while the child is most malnourished and subsequently decreasing the treatment dosage as the child improves– the opposite approach to the control arm. This dosing regimen is hypothesized to be even more cost effective than the experimental group A regimen, but runs the risk of lower recovery rates and higher rates of relapse that should be tested.

### Moderate acute malnutrition intervention– trial 2

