Upon enrollment, children with MAM will be randomly allocated to one of three groups (Fig. 1), with either RUTF or ready-to-use supplementary food (RUSF) (depending on the arm) provided in a 14-day supply on a fortnightly basis until discharge. All aspects of treatment will remain identical across arms apart from the dosing and type of ready-to-use food provided, which will differ as follows:

• MAM standard of care (control) group. Children in this group will be dosed with one sachet of RUSF, providing 530–540 kcal, to consume daily until discharge. This reflects the current national standard of care in Ethiopia [20].

• MAM experimental group A. Children in this group will receive one sachet of RUTF to consume daily until discharge. This reflects the draft simplified emergency protocol for MAM treatment in Ethiopia. Testing this dosing regimen in a rigorous trial will provide local evidence about the safety, efficacy, and cost efficiency of this regimen for food insecure contexts within Ethiopia (and possibly outside the country as well). This regimen would be expected to have a similar efficacy as the standard of care and simplify tasks for health workers and supply chains. A review of costing data across a range of suppliers suggests that the cost of RUTF is 5–20% higher than RUSF (depending on the manufacturer [22, 23]) and thus the marginal cost for treatment, once comprehensive costs of a MAM treatment program are included, may be relatively small. The 2023 WHO guidelines also acknowledge the likely equivalence between RUTF and RUSF in the effectiveness for achieving initial nutritional recovery in the treatment of MAM [5]. This would be one of the first trials to test this hypothesis prospectively.

• MAM experimental group B. Children in this group will receive two sachets of RUTF to consume daily until discharge. This reflects the draft simplified emergency protocol for SAM treatment in Ethiopia. Using this same regimen for MAM in addition to SAM would be a vast simplification for frontline health workers and for the health system in terms of demand planning and purchasing at scale. The cost per day of food would certainly be higher in this regimen, but a faster time to recovery may negate the higher daily cost. The benefits in terms of relapse rates and growth may also be greater with this regimen.

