Only a small body of evidence exists regarding the experimental dosing regimens being tested for SAM treatment. There remains equipoise in terms of the interventions’ effectiveness, given the lower quantity of RUTF that most children will receive and some experience showing higher rates of stunting following discharge; however, the potential for significant cost savings, increased coverage, and simplification for frontline health workers may make these modified dosing schedules a worthwhile pursuit nonetheless. We hope that the development of cost-efficiency models incorporating the data generated by these trials will help provide policymakers with the information they need to make fully informed decisions as they balance these conflicting imperatives.

The experimental dosing regimens we will investigate for children with MAM have not been previously studied as far as we are aware, and include one experimental arm putting to the test a new WHO recommendation that RUTF may be used instead of RUSF for MAM [5]. While it would seem rather obvious that RUTF would be just as effective as RUSF, given that RUTF has an even better mix of complete protein than RUSF, its lower micronutrient content and less energy per sachet makes its presumed effectiveness less than guaranteed. The third experimental arm for MAM takes quite a different approach from the previously tested regimens of *reduced* dosage, instead opting for an increased dosage using 2 sachets (1000 kcal) of RUTF daily. The hypothesis here is that, by significantly increasing the amount of treatment food consumed on a daily basis, the length of stay might be significantly shortened, thereby saving financial costs overall and also decreasing the morbidity burden these children suffer while acutely malnourished if they are able to recover quickly.

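### The SAM trial hypothesises group B against group A, but the article names only comparisons with control

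*Protocol article*

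**What the plan says.** Two places in the protocol article name the comparisons. The section on sample size for trials 1 and 2 describes the powered objective, recovery by 16 weeks, as "comparing each intervention group individually against the standard of care (control) group". The Statistical analyses section extends this to everything else: "Standard statistical approaches will be used in each of the three trials to analyze each intervention arm independently in comparison to the control arm".

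The section on the SAM intervention (trial 1) poses a different contrast for group B: "This dosing regimen is hypothesized to be even more cost effective than the experimental group A regimen". The sentence continues: "but runs the risk of lower recovery rates and higher rates of relapse that should be tested".

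The cost-effectiveness section calculates cost per child treated, cured, sustaining recovery and failing to sustain it for every arm. It allows for sensitivity analyses on costs and outcomes. It states no difference between B and A.

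In the MAM intervention (trial 2), the control arm is described thus: "Children in this group will be dosed with one sachet of RUSF, providing 530–540 kcal, to consume daily until discharge". Group A is described thus: "Children in this group will receive one sachet of RUTF to consume daily until discharge". Group B receives two RUTF sachets a day. On replacing RUSF with RUTF, the Discussion says of RUTF that "its lower micronutrient content and less energy per sachet makes its presumed effectiveness less than guaranteed".

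**The concern.** The article does more than leave a detail to a fuller document: it states which contrasts will be analysed, and that set leaves out the one on which SAM group B's stated advantage rests. If only arm-versus-control results are produced, a ministry choosing between A and B has two separate verdicts, and these can mislead in two ways. One arm may meet the margin and the other miss it without evidence that they differ. Or both may meet it, and the less costly regimen is taken as equally good although the data show that it recovers fewer children. Cost per child cured has the recovery rate in its denominator, so a cost-effectiveness claim for B over A also depends on the B-minus-A difference in recovery and its uncertainty.

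The MAM trial raises a narrower point. B versus control changes the product and the daily amount together, so that comparison cannot say how much of any effect is due to the amount.

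**Working it through.** **Inputs from the article.** Recovery 75%; margin 6 points; α 0.05, sidedness not stated; power 80%; 10% inflation; 798 per arm; equal allocation (blocks of 18, six per arm). Because sidedness is not stated, results are given for a 95% CI, with one-sided 5% in brackets.

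**The article's own figure.** The two-proportion formula with pooled variance, one-sided 0.05, 75% against 69%, is

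n = [1.645·√(2·0.72·0.28) + 0.842·√(0.75·0.25 + 0.69·0.31)]² / 0.06² ≈ 692.

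The continuity correction gives 725, and 725 × 1.10 = 797.5, so 798. The same route gives 465 and 307 for margins of 8 and 10 points (stated: 462 and 305). The sample size is not in dispute.

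**Precision of B minus A.** With equal allocation it matches that of each comparison with control:

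1.96·√(2·0.75·0.25/798) = 0.0425, about 4.2 points (4.5 with 725 evaluable).

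**Case 1: control, A and B all at 75%.**
- SE of a difference = √(2·0.75·0.25/798) = 0.0217.
- Each arm meets the margin with probability Φ(0.06/0.0217 − 1.96) = 0.79 (0.87).
- The two tests share a control arm, so the joint result was simulated: 400,000 trials, independent binomials, Wald intervals.
- Exactly one of A and B meets the margin in 24% (17%) of trials.

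**Case 2: control 75%, A 79%, B 73%.** The rates for A and B are assumptions chosen for illustration.
- A almost always passes, so the probability that both pass is close to B's own: Φ(0.04/√((0.1875 + 0.1971)/798) − 1.96) = Φ(−0.14) = 0.45 (0.57). Simulation gives 45% (57%).
- The direct B-minus-A 95% CI excludes zero with probability Φ(0.06/√((0.1659 + 0.1971)/798) − 1.96) = Φ(0.85) = 0.80.
- Both arms pass while the direct contrast shows B worse in 30% (40%) of trials.

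**With 725 per arm** the pattern is the same: 27% (20%) for case 1; 41% (54%) both passing and about 76% direct detection for case 2.

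**What the B-minus-A contrast could carry.** At 75% in both arms and a 6-point margin, its non-inferiority power with 798 per arm is 79% (87%) unadjusted. If α were split over three comparisons it would be 65% (74%). It is therefore useful as an estimate, but the trial was not sized for a third confirmatory test.

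**MAM arms side by side.** Control: one RUSF sachet. A: one RUTF sachet. B: two RUTF sachets. A versus control changes the product, with a small energy difference. B versus control changes product and amount. Only B versus A holds the product fixed.

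**The case against.** Several points on the other side stand.

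- **A reader might infer that B versus A will never be analysed.** The article does not support that. It names the powered and general comparisons without excluding others, it foresees multiple comparisons, and the analysis plan, which may hold secondary contrasts, is not shown.
- **The explicit B-versus-A hypothesis concerns cost-effectiveness.** The cost section gives costs per outcome for every arm, with sensitivity analyses, so A and B can be set side by side. What remains is that no B-minus-A difference in recovery is named to support such a claim.
- **The recovery and relapse risk has no comparator of its own.** Group A is the only arm named in that sentence, but the sentence before contrasts the regimen with control. B versus control also bears on the risk.
- **A reader might infer that the MAM comparison is confounded and so invalid.** It is not. The article states no MAM hypothesis of B against A and presents B as a whole regimen. B versus control is the right comparison for a programme choosing between that regimen and standard care. The limit applies only to claims about dose alone.
- **The simulated figures show no error in the primary test.** They follow from ordinary power applied to two tests with a shared control, and mislead only someone who ranks arms by pass or fail. The planned 95% CIs would show a gap such as 79% against 73%. But they would be intervals against control, and overlap between them does not measure the uncertainty of B minus A.
- **Relapse is not a simple extension.** Only recovered children are offered the post-recovery trial, so B minus A among them conditions on an outcome of treatment and is not a purely randomised contrast.

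**Conclusion.** The concern holds in a limited form. The article poses a SAM contrast of B against A, yet its named comparisons are with control only, and two verdicts against control cannot answer that question. The primary comparisons are randomised and valid.

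The 24% (17%) figure rests on the article's own planning values with all arms equal. The 45% (57%) and 80% figures rest on assumed recovery rates of 79% and 73% and show what is possible, not what is expected. Sample size does not explain the omission, since B minus A is as precise as each planned comparison. The change is worth making in the SAM trial and optional in the MAM trial.

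**What to change.** Keep each arm versus control as the powered comparison. Add to the Statistical analyses section, or confirm in the analysis plan:

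1. **SAM trial.** One pre-specified secondary estimate: the group B minus group A risk difference in recovery by 16 weeks, with 95% CI, by intention to treat, outside the α of the primary tests.
2. **Basis for claims.** Any statement that B is better, worse or more cost effective than A rests on this estimate, together with the incremental cost from the cost sub-study, and not on which arm met the margin.
3. **Relapse.** A B-minus-A comparison either uses all randomised children (for example, recovery sustained at 24 weeks after recovery, with non-recovery counted as failure) or is labelled as conditional on recovery.
4. **MAM trial (optional).** Report the same estimate, and rest any statement about dose alone on B versus A. B versus control remains the regimen comparison.

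The cost is a few sentences and one extra estimate per trial. No more children are needed and the primary tests do not change. The drawback is that B minus A is secondary and not sized for its own non-inferiority claim, so it should be reported as an estimate with its interval.
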